**Fig. 1 Fig1:**
[figure not shown]
Conservative management to clavicle fractures: **a** Figure-of-eight bandage. **b** Simple arm sling

In contrast to fractures at other skeletal sites, there are only few randomised trials which have compared either conservative or surgical approaches to the management of clavicle fracture. In addition, the available evidence from isolated trials is limited regarding the effectiveness of the different methods of surgical and conservative interventions [16–18].

Lenza et al. [16] concluded that evidence of only two clinical trials published in the 1980s [7, 19] is insufficient to determine the effects (benefits and harms) of the different methods of conservative (non-operative) treatments for acute (treated soon after diagnosis) middle-third clavicle fractures in adults. A search strategy, updated in January 2014, did not find any new comparative studies on conservative interventions for treating clavicle fractures.

Current literature reinforces the view that the best conservative treatment for middle-third clavicle fractures in adults is controversial. A recent survey indicates that most US surgeons prefer to use a simple sling rather than the figure-of-eight bandage for conservatively treating their patients (94 % prefer the simple sling versus 6 % prefer the figure-of-eight bandage) [20]. In contrast, a survey on conservative treatment of clavicle fractures in Germany concluded that the simple clavicle fractures are treated in a nonsurgical way and orthopaedic surgeons prefer the use of the figure-of-eight bandage in 88 % of cases [21].

Therefore, there is a need to investigate which would be the best intervention (considering functional endpoints and adverse effects) in patients with clavicle fractures. Since nonsurgical treatments are the most prevalent in current clinical practice, the authors of this study chose to evaluate the effects (benefits and harms) of conservative interventions: the figure-of-eight bandage versus the arm sling, for treating middle-third clavicle fractures.

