#### Secondary outcomes

Modified University of California at Los Angeles (modified - UCLA) [30, 31], validated and translated into Portuguese in Brazil [32]Pain measured on a 0 to 100 Visual Analogue Scale (VAS) (with 0 indicating no pain and 100 indicating maximum pain) [33, 34]. As reported in the literature, a clinically important change will be considered as a 30 % or more change in pain score [35, 36]. The total of analgesic consumed by the patients during the follow-up will be analysedTreatment failure will be considered as outcome in those participants who will need (or are being considered for) a surgical intervention (e.g. symptomatic nonunion or malunion with intractable pain). Although studies evaluating patients with fractures without displacement reported low rates of nonunion (about 0.03 %) [5, 6, 15], studies involving patients with displaced fractures found nonunion rates of up to 15 % [37–39]. Therefore, we expect that between 5 % and 10 % of our participants might exhibit symptomatic nonunion during follow-up period. The patients who experience this complication during follow-up will be treated surgically with open reduction and internal fixation with a pre-contoured locking plate placed on the superior surface of the clavicle, and bone grafting when necessaryAdverse events and effects will be evaluated by the following parameters: (a) cosmetic results: perception of deformity or asymmetry (dichotomous data); (b) asymptomatic nonunion (i.e. the fracture has not radiographically healed, although pain is absent); (c) stiffness/restriction of the shoulder movement (compared with contralateral side). We will also address any possible adverse event reported by participants.In 1986, the American Food and Drug Administration (FDA) defined nonunion to be ‘established when a minimum of 9 months has elapsed since injury and the fracture shows no visible progressive signs of healing for 3 months’. However, these criteria cannot be applied to every fracture [37]. Even though nonunion of the clavicle has not been definitively defined in the literature so far, many investigators agree that a diagnosis can be made if consolidation does not happen within 6 months after the injury [38–40]. The verification of the nonunion is made when there is clinical or radiographic evidence showing that healing has ceased and that union is highly improbable. We shall apply 6 months as the criterionNumbers returning to previous activities (work, sport, activities of daily living), including time to return

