### Data collection and analysis

#### Sample size

Sample size estimations were performed before patient recruitment. The main variable used was the DASH questionnaire. Type I error was pre-established as 5 % (95 % confidence interval) and type II error as 10 % (power of 90 %) with a population standard deviation of 15 %.

In order to calculate our sample size, we used the mathematical method described in the formula below:$$ \mathrm{n}=\left[{\left(\mathrm{Z}\upalpha /2+\mathrm{Z}\upbeta \right)}^2\times {\upsigma}^2\right]/{\upvarepsilon}^2, $$

where Z*α*/2 is the critical value *α* from the standard normal distribution with upper tail; Z*β* is the critical value *β* from the standard normal distribution; *σ* is population standard deviation; *ε* is the difference in the DASH questionnaire, which was assumed to be clinically relevant (10 points = minimal clinically important difference) [28, 42].

Thus, assuming the values described in the text, we have anticipated that 50 participants would be required in each group. Allowing for approximately 10 % loss to follow-up at 12 months, we aim to recruit a total of 110 patients.

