#### Data analysis

Demographic and baseline data will be summarised in the two study groups presenting number in each category and percentages of the number of patients in each group for categorical variables and presenting means and standard deviations or medians and quartiles for continuous variables. If we observe some clinically important imbalance between groups regarding to baseline variables we will adjust for them in the main analysis.

Patients, who for any reason may require additional interventions as part of their treatment, will be followed up, and their results will be included in the group into which they had initially been randomised, according to the intention-to-treat principle.

The primary outcome (DASH score) and the secondary outcomes (modified UCLA and VAS scores) will be analysed graphically. We will apply generalised mixed models in the intervention groups (two levels) and time-point assessments (seven levels) as fixed effects. To evaluate the effect of surgical interventions required due to treatment failure in the DASH score a similar model will be adjusted including the effect of surgery (two levels). In this analysis, patients who are undergoing surgery will have the data analysed up to the last assessment before surgery.

Secondary outcomes: treatment failure, adverse events and return to activities will be analysed individually by the chi-square test. The time to return to previous activities will be analysed by a Kaplan-Meier curve and Cox proportional hazard regression. The total analgesic amount consumed by the patients during the follow-up will be analysed by comparing study groups using the Mann-Whitney test.

To handle the effects of missing data we will describe patterns of missingness in the study groups and use the model-based method of multiple imputation to replace missing data.

The significance level of 5 % will be adopted in the analysis of the primary outcome and 1 % in the secondary outcomes, to avoid chance of statistical significance due to multiple tests.

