According to current evidence from a systematic review, there is very limited evidence from two single trials regarding the effectiveness of different methods of conservative interventions for treating clavicle fractures [16]. The reported results in the literature regarding the outcome of conservative treatment of middle-third clavicle fractures are controversial [5, 46]. In addition, as a conclusion of the most updated Cochrane systematic review [16], randomised controlled trials comparing contemporary conservative interventions, such as an arm sling versus the figure-of-eight bandage, for clavicle fractures are warranted. Consequently, we expect that our present study will provide conclusive results that can be readily used in clinical practice and offer evidence-based approaches for the conservative treatment of middle-third clavicle fractures.

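### The 1% significance level for secondary outcomes also covers treatment failure and adverse events, where it makes missing a real excess of harm more likely

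*Protocol article*

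**What the plan says.** All statements are in the protocol article.

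- **Data analysis** sets the levels: "The significance level of 5 % will be adopted in the analysis of the primary outcome and 1 % in the secondary outcomes". The stated reason is to limit chance significance from multiple testing.
- The same section gives the method for harms: "treatment failure, adverse events and return to activities will be analysed individually by the chi-square test".
- **Secondary outcomes** lists treatment failure (surgery needed or under consideration) and adverse events (perceived deformity, asymptomatic nonunion, stiffness), so both fall under the 1% level. The only rate it expects for this trial is for one component of failure: "we expect that between 5 % and 10 % of our participants might exhibit symptomatic nonunion during follow-up period".
- **Sample size** uses DASH alone: "we have anticipated that 50 participants would be required in each group", and "Allowing for approximately 10 % loss to follow-up at 12 months, we aim to recruit a total of 110 patients".
- **Background** gives the purpose as to "investigate which would be the best intervention (considering functional endpoints and adverse effects) in patients with clavicle fractures". **Discussion** adds: "we expect that our present study will provide conclusive results that can be readily used in clinical practice".

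**The concern.** A stricter level buys protection against false alarms and pays for it in power. For secondary efficacy outcomes that is a reasonable trade. For harms the balance differs: overlooking a real excess of failed treatment, with patients going on to surgery, is usually worse than flagging one that later proves to be chance. The article applies the same 1% to both without distinction, although its purpose includes adverse effects. A sizeable excess of failures in one arm could therefore be labelled non-significant by the plan's own rule, even when the data point clearly to harm.

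**Working it through.** **Inputs.** From the article: 50 evaluable per arm, 110 recruited (55 per arm if split equally), chi-square test, 1% for secondary and 5% for primary outcomes, symptomatic nonunion in 5 to 10% of participants overall. Assumed here: two-sided tests (as in the sample size formula), treatment failure about as common as symptomatic nonunion, and the size of the difference between arms, since the article gives none for harms. The main case is 5% against 15%, which averages (5 + 15)/2 = 10%, the upper end of the stated range.

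**The plan's own figure.** For DASH, n per arm = 2 × (1.960 + 1.282)² × 15²/10² = 47.3, or 48.3 with the t distribution. The stated 50 agrees and gives about 91% power. (The printed formula lacks the factor 2 and taken literally gives 23.6; the stated 50 matches the usual two-sample form.) The primary comparison is therefore adequately sized. No power is stated for harms.

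**Power for treatment failure.** With i and j failures in two arms of n, and m = i + j, the uncorrected Pearson statistic is X² = 2n(i − j)²/[m(2n − m)]. The binomial probabilities of all tables with X² at or above 6.635 (1% level) or 3.841 (5% level) were summed:

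| True failure rates | Power at 1%, n = 50 (55) | Power at 5%, n = 50 (55) |
|---|---|---|
| 2.5% vs 7.5% | 3% (4%) | 18% (20%) |
| 5% vs 10% | 3% (4%) | 14% (16%) |
| 5% vs 15% | 16% (19%) | 39% (42%) |
| 5% vs 20% | 38% (43%) | 66% (69%) |
| 10% vs 20% | 11% (13%) | 30% (31%) |
| 7.5% vs 22.5% | 31% (37%) | 59% (61%) |
| 10% vs 30% | 49% (55%) | 73% (77%) |

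For 5% against 15%, the 1% rule removes more than half of the power available at 5%: (39.3 − 15.6)/39.3 = 60% at n = 50. A continuity-corrected or Fisher test at 1% has less still, 8% and 10% at n = 50.

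**How much is due to the 1% level.** The usual two-proportion formula, n = [z(α/2)√(2p̄(1 − p̄)) + z(β)√(p₁(1 − p₁) + p₂(1 − p₂))]²/(p₂ − p₁)², with 5% against 15% and 80% power, gives:

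- at 1%: (2.576 × 0.4243 + 0.842 × 0.4183)²/0.01, about 209 per arm;
- at 5%: (1.960 × 0.4243 + 0.842 × 0.4183)²/0.01, about 141 per arm.

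Both are far above 50, so sample size is the main cause of the low power and the 1% level makes it worse.

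**A concrete result.** With 12/50 against 3/50 failures, X² = 100 × 9²/(15 × 85) = 6.35 and p = 0.0117, which is non-significant at 1%. The Wilson limits are 14.3 to 37.4% and 2.1 to 16.2%. Newcombe's interval for the 18-point difference is then:

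- lower: 18 − √(9.7² + 10.2²) = about +4 points;
- upper: 18 + √(13.4² + 3.9²) = about +32 points.

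With 3/50 in each arm, the interval is −11 to +11 points; with 5/50 in each arm, −13 to +13.

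**The case against.** A reader might infer that the plan treats p > 0.01 on a harm outcome as evidence of equal safety, or that it promises a conclusive answer on harms. The article supports neither. It never says how a non-significant harm result will be read. The Discussion speaks of an expectation, in text about effectiveness, and does not mention harms there. Nor does naming a test and a level mean that only p-values will be reported: effect measures and intervals may stand in an analysis plan that is not shown, and their absence from a condensed article is no fault.

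It is also tempting to say that any tripling of failure would be missed more than 80% of the time. That holds if the lower arm is at about 5% or less, as it would be if 5 to 10% is the overall rate. If the lower arm were at 10%, a tripling to 30% would be missed 51% of the time at 50 per arm and 45% at 55. The expected rate is for symptomatic nonunion; treatment failure is defined somewhat more widely, and no rates are given for deformity, asymptomatic nonunion or stiffness. A commoner harm would be better served: 20% against 50%, as an assumption, has 73% power at 1% with 50 per arm.

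Finally, low power for a rare secondary outcome is ordinary, the article is open that DASH sized the trial, and 1% has a stated reason. All of this stands. What it does not answer is that the published rule applies that reason to harms, where it worsens the error that matters more. An analysis plan consistent with the article would inherit that level.

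**Conclusion.** The point holds in limited form. It concerns a stated choice, the 1% level for harms, and not a gap in reporting. Under the assumption of 5% against 15% failure, that choice lowers the chance of detection from 39% to 16% at 50 per arm (from 42% to 19% at 55), and it would label an observed 24% against 6% non-significant although the 95% interval excludes zero. The size depends on the assumed rates, and the calculation does not extend to adverse events for which no rate is given. Moving harms to 5% would help but would not make the comparison precise: 5% against 15% would still be missed about 60% of the time. This is a worthwhile, inexpensive improvement; it does not invalidate the trial or its primary analysis.

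**What to change.** In Data analysis, exempt treatment failure and adverse events from the 1% level. For these outcomes, report the between-arm risk difference with a 95% confidence interval (for example Newcombe), with the chi-square p-value beside it as descriptive. State that the conclusion on harms rests on the interval and that a non-significant test will not be taken as no difference. Keep 1% for the secondary efficacy outcomes: modified UCLA, VAS pain, return to activities and analgesic use. In the Discussion, confine the expectation of conclusive results to the DASH comparison and say that harm comparisons are estimates of limited precision, about ±11 to ±13 points at equal failure rates of 6 to 10%.

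The cost is wording only, with no extra patients or data. The downside is that harm outcomes lose the 1% protection against chance findings, so an isolated low p-value among several adverse-event comparisons needs cautious reading.

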## Discussion

This protocol describes a pragmatic trial design, which has been chosen because of its direct applicability to clinical practice. Thus, this study includes design characteristics known to minimise bias [43]. Participants will be assigned using a concealed random procedure, assessments and data analysis will be blinded and we will use the intention-to-treat analysis. Consequently, our inclusion criteria will reflect the variety of patient presentations that would be encountered by general orthopaedic surgeons in the clinical setting. In addition, our primary outcome is a validated Patient Reported Outcome Measures (PROMs) for the shoulder.

Currently, acute displaced middle-third clavicle fractures are conventionally treated by conservative interventions with high expectation of fracture union and patient satisfaction. However, a recent multicentre randomised controlled trial demonstrated better functional outcomes with surgical interventions, but the authors did not support routine primary surgical treatment for these fractures [44].

A small randomised controlled trial was recently published [45]; it included 60 participants with an acute, isolated middle-third clavicle fracture. The authors compared the broad arm sling with the figure-of-eight bandage; their outcome measures were pain, Constant and American Shoulder and Elbow Surgeons scores and degree of radiographic union. The study concluded that both techniques provided acceptable functional and radiological outcomes for treating clavicle fractures. However, the broad arm sling was significantly more comfortable in the first 3 days of treatment. One weakness of that study was the small sample size and the additional loss of patients in the final follow-up period (two patients in the broad arm sling group and seven patients in the figure-of-eight bandage group), which may have affected the results, since the sampling loss was greater in the figure-of-eight bandage group. The study had other sources of bias. First, the study design did not permit blinding of participants, orthopaedic surgeons and outcome assessors; although failure of blinding can have a serious effect on study outcomes, the authors were unable to perform it. Secondly, the function outcomes (Constant and American Shoulder and Elbow Surgeons scores) were not validated for use in a number of settings (mainly Constant score) and these scores may not be specific for use as an outcome in clavicle fractures [45].

According to current evidence from a systematic review, there is very limited evidence from two single trials regarding the effectiveness of different methods of conservative interventions for treating clavicle fractures [16]. The reported results in the literature regarding the outcome of conservative treatment of middle-third clavicle fractures are controversial [5, 46]. In addition, as a conclusion of the most updated Cochrane systematic review [16], randomised controlled trials comparing contemporary conservative interventions, such as an arm sling versus the figure-of-eight bandage, for clavicle fractures are warranted. Consequently, we expect that our present study will provide conclusive results that can be readily used in clinical practice and offer evidence-based approaches for the conservative treatment of middle-third clavicle fractures.

## Trial status

This trial started recruiting patients in November 2015.

## Abbreviations

CONSORT: Consolidated Standards of Reporting Trials
DASH: Disability of the Arm, Shoulder and Hand
FDA: American Food and Drug Administration
PROMs: Patient Reported Outcome Measures
UCLA: University of California at Los Angeles
VAS: Visual Analogue Scale
